### Study phases

The INTEGRA study is divided into two distinct phases. Phase 1 is a qualitative research study, which is aimed at identifying viable strategies to overcome barriers to treatment; these strategies have been included in the intervention study (phase 2). Phase 2 is a controlled, non-randomized, interventional, pragmatic study that involves primary care centres in 3 regions in Catalonia (Lleida, Girona and Barcelona).

#### Phase 1: Qualitative study

##### Design

A qualitative study with a phenomenological approach was conducted to identify the barriers and facilitators for the management of poorly controlled T2DM patients. This approach was taken in order to identify psychosocial factors influencing glycaemic control. Briefly, we collected information on the patient’s perception on the communication of the diagnosis, cognitive representation of the disease (knowledge, cause, symptoms, duration, consequences and control of the disease), emotions associated with the disease (e.g., fears or worries about the future), and their cognitive and emotional attitudes regarding strategies to control diabetes (diet, physical activity, and pharmacological activity). Finally, patients described their perceived relationship with the health-care professionals and gave their input regarding the design of the INTEGRA study (e.g., visit schedule or use of information and communication technologies). The results of this phase of the study were used to draw recommendations and to design strategies in order to optimize the patient’s adherence and disease control during the intervention phase of the INTEGRA study. Thus, other components that may be needed for the intervention, such as the use of Information and Communication Technologies like internet platforms or mobile applications, was also determined.

##### Recruitment strategies and participants

At each primary care centre, a liaison was selected to facilitate the communication between the centre and the research team. One member of the research team contacted the liaison at each primary care centre. These liaisons, together with the primary care professionals, identified the patients who meet the criteria of poor glycaemic control and contacted the potential participants.

##### Sampling

The sampling for the study was opportunistic [15]. Although not a theoretical sample, it was taken into account the following variables: gender, age, years of progression of T2DM, and type of treatment (oral antidiabetics, insulin, or a combination).

##### Techniques for generating information

A psychologist carried out 8 to 10 semi-structured individual interviews in each Primary Health Care Centre. This interview technique is especially useful when it is important to collect the subjective opinions of societal actors, and becomes even more valuable when wanting to explore diverse points of view that represent the different attitudes that might exist regarding the subject of investigation [16]. The interviews were audio-recorded and subsequently transcribed systematically and verbatim.

##### Analysis

A thematic content analysis was performed based on the information obtained from the interviews [17]. The data was analysed in the following manner: after successive readings of the transcribed interviews [18], the researchers attained some pre-analytical insight into the data. Next, four researchers conducted the following analytical steps: (a) identification of the relevant subjects and texts; (b) fragmentation of the text into units of meaning; (c) text codification with a mixed strategy: Leventhal model and emerging codes from the data; (d) creation of categories by grouping the codes based on the criterion of similarity; (e) analysis of each category; and (f) elaboration of a new text with the results. These results were subsequently discussed by the research team members until a consensus was reached (triangulation).

The results of the qualitative study have been published recently [19].

#### Phase 2: Interventional study

##### Design

A controlled, non-randomized interventional study that involves primary care centres of 3 health care districts in Catalonia (Lleida, Girona, and Barcelona).

##### Participants

The participants are T2DM patients with poor glycaemic control that meet all the inclusion criteria and sign the informed consent.

##### Inclusion criteria for primary health care Centres

The participating Primary Care centres must meet the following criteria to be eligible: I) experience of more than 5 years using the eCAP™ programme (electronic clinical records of Primary Care Centres in Catalonia) to optimize the use of the software as a source of information and intervention (warnings, alerts, etc.); II) centres with more than 10 general practitioners, to obtain a large number of study subjects; III) centres belonging to different health care areas, to increase external validity of the study; and IV) acceptance by the majority of professionals in the centre.

##### Intervention design

In each basic health area, two intervention groups and one control group were included. Two different interventions focused on treatment intensification, namely reducing inertia by professionals and reducing the possible barriers to treatment adherence have been implemented, one in each intervention group. In order to reduce inertia by primary care professionals, to get closer to the objectives of health control, and to allow reproducibility in the current context of primary care centers, the intervention was carried out through multiple integrated strategies. To improve the intervention replicability, the Template for Intervention Description and Replication guide was followed [20]. Each health care district has a contact in a hospital with a Department of Endocrinology who provides specialized support for professionals if needed.

#### Intervention group 1 (IG-1)

Intervention 1 consists of a comprehensive strategy with the following components:A specialized consultation carried out by a general practitioner and a nurse that will provide the participant with a complete assessment of their case, and a series of recommendations will be set for case management, together (only if required) with the specialized team from Endocrinology and Nutrition using a telematics communication system. The strategy recommendation includes management measures aimed at optimizing blood glucose, blood pressure, lipid profile, and other cardiovascular risk factors, as well as the detection of diabetes-associated complications following the guidelines of the Catalan Health Institute [21] and the guidance document of the Department of Health of the local government (Generalitat de Catalunya) [22].Basic training in clinical practice guidelines: consulting professionals will participate in workshops related to clinical practice guidelines, thus broadening the professionals’ knowledge base with regard to diabetes by providing them with an increased degree of autonomy in diabetes case management.Training of professionals in coaching: all professionals in the primary care centres will participate in a 7-h training programme for coaching to be able to impart practical theoretical content on the following subjects: strategies for active listening; strategies for communication without value judgement; support strategies to develop self-management skills for diabetes, hypertension, and hyperlipidaemia; strategies to provide social and emotional support; strategies to motivate lifestyle changes; strategies for medication adherence; and strategies to access community resources.The professionals will attend a 2-h training programme to update their training for reviewing the practical cases discussed in consultation using a coaching strategy point of view.Interventions based on patients’ SMS phone messages (sending a message 1 time / week during the first three months) to promote the change in behaviour and to maintain healthy lifestyle changes to improve diabetes control.

#### Intervention group 2 (IG-2)

Patients allocated to the IG-2 will receive the same personalized intervention described for the IG-1, without the monographic consultation (Fig. 1).

**Fig. 1 Fig1:**
[figure not shown]
Study flow chart. *Control group: usual clinical care with the usual control by the family doctor and nurse according to the current CPG protocol. +Intervention 1: Usual clinical care with the usual control + Monographic consultation + Basic training in clinical practice guidelines + Training in coaching + 2-h training program to update the coaching strategy + Intervention based on patients SMS phone messages. ++Intervention 2: Usual clinical care with the usual control + Basic training in clinical practice guidelines + Training in coaching + 2-h training program to update the coaching strategy + Intervention based on patients SMS phone messages. m: months

#### Control group

The control group will consist of a randomized selection of patients who meet the inclusion criteria and have the same sociodemographic and clinical characteristics as the patients from the intervention groups, including the three participating health care districts. Patients allocated in this group will receive routine clinical care with the usual control by the family doctor and nurse according to the current Catalan Health Institute protocol. The data of patients in the control group will be obtained from the electronic medical record (SIDIAP) database [23]. The inclusion period for the control group will be from 9 December 2015 (the date when the first patient entered the study) until 31 October 2017 (end of the recruiting period). Data on diabetic status, glycaemia and all other study variables that were recorded in the electronic health records for patients in the intervention groups will be extracted from the SIDIAP database for 12 months for each patient. Participants will be followed up until they experience the outcomes of interest, die, leave the SIDIAP database (e.g., change of address) or complete the follow-up (31 October 2018). If the intervention groups reach the study sample earlier than 31 July 2017, the data for the control group will be followed until 12 months from the date when the last patient would be enrolled in the intervention group.

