### Statistical analysis plan

For data analysis, the IG-1, the IG-2, and the control group will be compared. All analyses will be carried out using bilateral tests with a nominal significance level of 0.05. However, if the comparisons obtain a *p*-value of less than 0.10, they will also be discussed as indicative of trends. Initially, basal characteristics of all groups will be evaluated to establish homogeneity in age, socio-demographic, comorbidities, laboratory parameters, concomitant medication and diabetes complications. An initial, descriptive comparison between groups of all variables will be performed to evaluate their baseline balance. Statistical significance will be assessed by the chi-square or t-test between the groups. Exploratory analyses will be applied when necessary.

The main variable is set as the difference in mean HbA1c values between the final visit and baseline. The difference will be evaluated in terms of the evolution of HbA1c as contrasted between groups by paired t-Student, or if the assumption of normality is not met for the right non-parametric.

If differences in the characteristics of the patients in each group are observed in the descriptive section of the study, a linear regression of the main variable (parameter evolution during the study) will be adjusted. This linear regression adjusted for the variables identified in the descriptive section, or the ability to adjust the model by setting a propensity score, will be evaluated. For all models, the distribution of waste will be studied, as well as the coefficient of determination (R2), to check for the correct setting.

As was done in Vinagre et al. [4], a subgroup analysis will be performed by a) gender (male / female), b) age: < age 65 / ≥ 65, and c) according to HbA1c control levels (< 10% / ≥ 10%).

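### The control group's data have conflicting end points; if extraction stops at 12 months per patient, the usual-care month-12 HbA1c can only come from a routine test at or before month 12

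*Protocol article*

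**What the plan says.** All of the following is in the protocol article.

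- **Control group, care.** "Patients allocated in this group will receive routine clinical care with the usual control by the family doctor and nurse". No study visit is planned, and all data come from the SIDIAP database.
- **Control group, inclusion.** "The inclusion period for the control group will be from 9 December 2015" and runs "until 31 October 2017 (end of the recruiting period").
- **Control group, first end point.** Study variables "will be extracted from the SIDIAP database for 12 months for each patient".
- **Control group, second end point.** Participants are followed until an outcome of interest, death, departure from the database, or until they "complete the follow-up (31 October 2018").
- **Control group, third end point.** If the intervention groups fill early, "the data for the control group will be followed until 12 months from the date when the last patient would be enrolled in the intervention".
- **Table 1 and its footnote.** Controls are assessed at months 0 and 12 from SIDIAP. IG-1 has visits at months 0, 3, 6 and 12, and IG-2 at months 0, 3 and 12. Both intervention groups have HbA1c at month 12.
- **Evaluation of the effectiveness in the three study groups.** Baseline is compared with 12 months. Time windows for accepted values are promised without widths. Either a cohort followed to 2018 or two cross-sections (2015 and 2018) may be used.
- **Statistical analysis plan.** The main variable is "the difference in mean HbA1c values between the final visit and baseline", and all three groups are compared.

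**The concern.** The main variable needs a final HbA1c at about the same time in every group. In IG-1 and IG-2 a scheduled visit supplies it, and in practice that visit can fall a little before or after month 12. A control has a value only if routine care happened to order one. Under the 12-month extraction sentence, a control tested at month 12.5 has no usable month-12 result from that test, so an earlier value stands in or there is none. The promised windows cannot repair this, because a window cannot accept a value that was never extracted. For controls, any window would be one-sided.

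The other two end points allow later values for most controls. The text therefore does not settle whether a result after month 12 may be used. At stake is whether the usual-care contrast compares like with like in time, and how many controls contribute to it.

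**Working it through.** **1. What the article gives.** It states no figure for the timing or availability of HbA1c in controls, so there is none to reproduce. Its allowance for loss is 20%, and that part of the sample size does reproduce. With SD 1.46, difference 1, two-sided alpha 0.05 and power 0.80, n = 33.46 per group. Then 33.46/0.8 = 41.8, i.e. 42; 42 × 1.7 = 71.4, i.e. 72; and 72 × 9 = 648.

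**2. The end points compared by date.**

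- 31 October 2017 to 31 October 2018 is 365 days. A control included on the last date has 12 months under either the extraction rule or the 31 October 2018 rule.
- 9 December 2015 to 31 October 2018 is 1057 days, or 1057/30.4375 = 34.7 months. A control included on the first date has 12 months under one rule and 34.7 under the other.
- The inclusion period is 692 days. If entry is uniform over it (assumption), the share with at least m months of data after month 12 under the 31 October 2018 rule is 1 − m × 30.4375/692. This gives 96%, 91% and 87% for m = 1, 2 and 3. Under the extraction rule it is 0% for every m.

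**3. Share of controls with a value in the window.** The testing interval and the window are assumptions, because the article gives neither. If tests come every T months with random phase, the share with a test in a window of L months is min(1, L/T). If intervals vary (gamma distribution, mean T, coefficient of variation 0.3), simulation gives the second pair of columns.

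| Mean interval T | Regular: months 9–12 | Regular: months 9–15 | Irregular: months 9–12 | Irregular: months 9–15 |
|---|---|---|---|---|
| 3 months | 100% | 100% | 88% | practically 100% |
| 4 months | 75% | 100% | 72% | 99% |
| 6 months | 50% | 100% | 50% | 88% |
| 12 months | 25% | 50% | 25% | 50% |

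With irregular testing, the share without a value in months 9–12 is 12% at 3-month testing, within the 20% allowance. It is 28% at 4 months, 50% at 6 and 75% at 12, all above the allowance.

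**4. Timing if the last value within 12 months is used instead.** With regular testing its mean time is 12 − T/2: month 10.5, 10, 9 and 6 for T = 3, 4, 6 and 12. With irregular testing it is month 9.8, 8.7 and about 6.6 for T = 4, 6 and 12. The control value is earlier than month 12 on average in every case.

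**5. Is power the problem?** No. Take the worst row: 216 × 0.25/1.7 = 31.8 effective controls, against 216 × 0.8/1.7 = 101.6 in an intervention group. The standard error is 1.46 × √(1/101.6 + 1/31.8) = 0.297, and power for a 1% difference is Φ(1/0.297 − 1.96) = 0.92. The issue is comparability in time and selective availability, not sample size.

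**The case against.** A reader might infer that control data are definitely cut at 12 months. The section does not settle this. Two later sentences run follow-up to a calendar date, and the 12-month phrase could be read as a nominal follow-up length. On the calendar-date reading most controls have ample data after month 12. This objection stands, and it is why the point is worded as a conflict with a conditional consequence.

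A reader might also infer that many controls have no value near month 12. No testing frequency is given. Under a hard cut, the modelled share without a value runs from 0% (3-month testing, 3-month window) to 92% (12-month testing, 1-month window). The random-phase assumption matters too. If each control's clock starts at an HbA1c test (the article does not state the index date), the mean last value at 12-month testing moves to month 9.4, but only 54% have any value by month 12.

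A third inference would be a bias of known direction in HbA1c, or selective loss of the worst-controlled patients. The article gives no HbA1c trajectory and no link between control and testing frequency, so neither can be shown.

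Finally, the Study design section makes IG-2 the control for IG-1 and calls the SIDIAP group an additional comparison. Both intervention groups have scheduled month-12 visits, so that contrast is untouched.

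It is fair to add that window widths may stand in a fuller plan, and their absence from the article is no fault. But a window defined there would still be one-sided for controls if extraction ends at month 12.

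**Conclusion.** The point holds in a limited form. The Control group section states end points for control data that differ by up to 22.7 months (34.7 − 12) for the same patient, and they must be reconciled. If the 12-month extraction governs, and for controls included on 31 October 2017 in any case, the final HbA1c in the SIDIAP group can only be dated at or before month 12. It will on average be earlier than in IG-1 and IG-2, and more often absent.

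The direction of the timing difference holds at every testing interval modelled. Its size is conditional: a 9–12 month window captures about 72% to 25% of controls at mean intervals of 4 to 12 months, against 99% to 50% for months 9–15, with little shortfall at 3-month testing. These figures rest on assumed intervals, a coefficient of variation of 0.3 and random phase. The effect on the HbA1c difference itself is not quantified. Only the three-group, usual-care comparison is exposed. The change is worth making because the stated rule gives a poorer contrast and is cheap to correct.

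**What to change.** 1. In the Control group section, state one end point for control data and remove the competing ones.
2. Extract SIDIAP data past month 12 by the width of the accepted window. For example, extract 15 months per patient, which puts the database end at 31 January 2019 for a control included on 31 October 2017.
3. Define month-12 HbA1c in all three groups as the value closest to month 12 within one symmetric window, for example months 9–15. Apply the same rule to lipids and blood pressure, and use it for the intervention groups in the three-group comparison.

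The 15 months and the 9–15 window are examples. The necessary parts are a single end point and the same symmetric window in every group.

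The cost is a longer extract from an existing database and one definition, with no change to patient care. The control extract is ready about three months later. Some controls will still lack a value if testing is infrequent: half of them at 12-month testing in the model above.

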##### Study variables

The variables are collected at different time-points during the study (Table 1). These include: sociodemographic variables (age, sex), anthropometric variables (height, weight, BMI, blood pressure), clinical variables (drugs and dosages), smoking habits (smoking, non-smoker, ex-smoker), presence of multiple disorders (Clinical Risk Group and identified in the computerized patient clinical history and the number of health problems as a proxy asset of multi-morbidity), presence of microvascular complications (diabetic retinopathy, diabetic nephropathy, and diabetic neuropathy), presence of macrovascular complications (ischaemic heart disease, stroke, peripheral vascular disease, and heart failure), laboratory variables according to the standard procedures of the laboratory of reference (HbA1c, blood count, renal function- creatinine, glomerular filtration rate, urinary excretion of albumin), liver function (Alanine Aminotrasferase (ALT), Aspartate Aminotransferase (AST), alkaline phosphatase, Gammaglutamil transferase (GGT)), lipid profile (total cholesterol, HDL-C, triglycerides, LDL-C, and non-HDL-C), and episodes of severe hypoglycaemia (episodes of hypoglycaemia that require the intervention of a third party for recovery will be recorded).

**Table 1 Tab1:** Study timeline, variables and procedures

	IG-1 and IG-2					Control group	
Data collected	Assessment (months)				Source	Assessment	Source
	0	3	6	12		Month 0 & Month 12	
Inclusion/Exclusion criteria	1 + 2	1 + 2	1	1 + 2	e-CRF	§	SIDIAP
Sociodemographic variables and comorbidities: *1. Age, height, gender, weight, BMI, duration of T2DM, medication (active component and dose),* etc.*...* *2. Pluripathology, clinical risk group*	1 + 2	1	1	1 + 2	eCAP	§	SIDIAP
Main variable: HbA1c	1 + 2	1	1	1 + 2	e-CRF eCAP	§	SIDIAP
Lipid profile and other laboratory variables: Total cholesterol, HDL, LDL, triglycerides, non-HDL, urea, creatinine, glomerular filtration rate, urine albumin, AST, ALT, FA, GGT. Systolic and diastolic blood pressure	1 + 2	1	1	1 + 2	eCAP e-CRF	§	SIDIAP
Smoking habit	1 + 2	1	1	1 + 2	eCAP e-CRF	§	SIDIAP
Sedentary lifestyle	1 + 2	1 + 2	1	1 + 2	e-CRF		
Detection of macrovascular complications *Ischaemic heart disease, stroke, peripheral artery disease, heart failure*	1 + 2	1	1	1 + 2	eCAP e-CRF	§	SIDIAP

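### If the intervention groups fill before 31 July 2017, the control-group rule shortens control data without closing control entry, so late-entering controls could not have the promised 12 months (minor, conditional)

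*Protocol article*

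**What the plan says.** All the dates are in the Control group section of the protocol article.

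- **Entry.** "The inclusion period for the control group will be from 9 December 2015 (the date when the first patient entered the study) until 31 October" (the closing year is 2017). The closing date carries a gloss: "until 31 October 2017 (end of the recruiting period").
- **Data per patient.** The study variables "will be extracted from the SIDIAP database for 12 months for each patient".
- **Default end.** Unless something ends follow-up sooner, patients "complete the follow-up (31 October 2018").
- **Early completion.** "If the intervention groups reach the study sample earlier than 31 July 2017, the data for the control group will be followed until 12 months"; the sentence ends by counting "12 months from the date when the last patient would be enrolled in the intervention group".

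Three other places show what the control data are for. Table 1, under Study variables, has only two control assessments: "Month 0 & Month 12". The section on evaluating effectiveness in the three study groups compares baseline with 12 months. The Statistical analysis plan section says: "The main variable is set as the difference in mean HbA1c values between the final visit and baseline".

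**The concern.** The first three statements fit together; the fourth fits them only if control entry also closes early, and the section does not say that it does. With the fixed entry date left in place, a control can enter after the last intervention patient and still have data cut off 12 months after that patient's enrolment. The promise of 12 months for each patient then cannot be kept.

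The effect falls on one group. Every intervention patient is enrolled on or before the date from which the 12 months are counted, so none is truncated by this rule. Controls have no scheduled value between month 0 and month 12. A truncated control is therefore either missing at month 12 or has an earlier HbA1c treated as the final one, which sets a shorter change against a 12-month change. Such controls would also enter in calendar months when no intervention patient was entering. In a non-randomized study, where comparability depends on how the control group is assembled, this is an avoidable source of bias.

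**Working it through.** **Inputs from the documents.** Control entry from 9 December 2015 to 31 October 2017, default end of follow-up 31 October 2018, early-completion trigger 31 July 2017 (all from Control group); 216 controls (Abstract); detectable difference 1% HbA1c, SD 1.46, 20% loss, design effect 1.7, two-sided alpha 0.05 (Sample size calculation).

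**Assumed, because the documents do not give them.** The date T of the last intervention enrolment, and uniform control entry over the window.

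**Step 1: the default schedule.** A control entering on the last day, 31 October 2017, and followed to 31 October 2018 has 365 days. The default keeps the 12-month promise for everyone.

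**Step 2: the early-completion rule.** For a control entering on date E, the data available are

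min(12 months, T + 12 months − E).

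If E is on or before T, this is 12 months. If E is after T, the shortfall is E − T. The longest shortfall is 31 October 2017 − T.

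**Step 3: illustration.** The entry window is 693 days, counting both ends. With uniform entry, the share affected is (31 October 2017 − T)/693.

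| Assumed T | Days of entry after T | Share of controls | Of 216 | Shortest data span |
|---|---|---|---|---|
| 30 July 2017 | 93 | 93/693 = 13% | 29 | 365 − 93 = 272 days (8.9 months) |
| 30 April 2017 | 184 | 184/693 = 27% | 57 | 365 − 184 = 181 days (5.9 months) |
| 31 January 2017 | 273 | 273/693 = 39% | 85 | 365 − 273 = 92 days (3.0 months) |

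If T is 31 July 2017 or later, the trigger is not met, the default end applies and no control is short.

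**Step 4: power.** The plan's own size is reproduced first: 2 × [1.46 × (1.960 + 0.842)/1]² = 33.5 per group; 33.5/0.8 = 41.8, so 42; 42 × 1.7 = 71.4, so 72.

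With 216 per group, the effective number is 216 × 0.8/1.7 = 101.6 per group and power for a 1% difference is 99.8%. Dropping the affected controls leaves 187 when T is 30 July 2017, an effective 88.0, and power 99.7%. When T is 31 January 2017 it leaves 131, an effective 61.6, and power 98.9%. Lost numbers are not the problem.

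**Step 5: with the rule repaired.** If entry closes at T, no E is later than T and the shortfall is zero for every control.

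**The case against.** The strongest reply is that the section nearly answers the point itself. The closing date is glossed as the end of recruitment, and the default end of follow-up is that date plus 12 months. The early rule keeps the same relation, so the natural intention is that both dates move together. The 12-months-per-patient sentence points the same way. This is a fair reading and probably the intended one. But entry is given as a calendar date, and the conditional sentence changes only how long data are followed. An extraction programmed from the text could keep the later entry date.

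A second reply is that the three-group evaluation section offers two routes: a cohort qualifying in 2015 and followed to 2018, or cross-sections in 2015 and 2018. Under the first no control enters late in 2017; under the second there is no individual follow-up to truncate. This narrows the point to an analysis built on the Control group section. It does not remove it, because that section sets control entry through October 2017 and a 2015-only cohort does not match that window.

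Four stronger readings are tempting, and the documents do not support them:

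- A reader might take the gap between 31 July and 31 October 2017 as an error. A trigger for finishing early has to precede the planned end, and between the two dates the default gives every control 12 months.
- A reader might take 13% to 39% as the expected loss. Those shares rest on assumed enrolment dates and uniform entry, and nothing in the article shows that the trigger was met.
- A reader might infer that the control group would fall short of 216 or be underpowered. Controls are drawn from a large database, so records can be replaced, and step 4 shows little loss of power even without replacement.
- A reader might infer that the main contrast is compromised. The Study design section makes IG-2 the control for IG-1 and describes the SIDIAP group as an additional comparison; the rule does not touch IG-1 versus IG-2.

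**Conclusion.** The Control group section is internally inconsistent in one conditional case. If the intervention groups filled before 31 July 2017, the fixed entry date, the 12 months promised per patient and the early end of control data cannot all hold. Controls entering after the last intervention enrolment would then lack a month-12 HbA1c or contribute a shorter change, in the control group only.

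That some controls could fall short follows from the dates alone. How many would do so cannot be known from the documents; the 13% at 30 July 2017 is an illustration. The consequence is unequal or missing follow-up, and poorer calendar alignment, in the comparisons with the SIDIAP group. Severity: minor.

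**What to change.** Replace the early-completion sentence with a rule that holds whenever recruitment ends: control inclusion closes on the date of the last intervention enrolment, 31 October 2017 at the latest, and each control is followed for 12 months from his or her own inclusion date. Apply this as a date filter in the SIDIAP extraction; any control already selected with a later inclusion date can be replaced by one from within the window.

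Under this rule control data end no later than 12 months after the last intervention enrolment, which is what the present sentence appears to aim for. The 31 July 2017 trigger is then no longer needed and can go, although it is not wrong in itself.

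The cost is one sentence and one filter. Reporting the actual date of the last intervention enrolment would also show whether the early-completion case ever arose.
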